|                                                      | 
Grade 3 or 4
 (Grade 3: serum creatinine <math>>3.0 \times</math> baseline; <math>>3.0</math> to <math>6.0 \times</math> ULN)
 
 (Grade 4: serum creatinine <math>>6.0 \times</math> ULN)
 | 
Permanently discontinue study drug/study regimen.
                                                                                                                                                                                                               | 
For Grade 3 or 4:
 
 
Carefully monitor serum creatinine on daily basis.
 
Consult nephrologist and consider renal biopsy if clinically indicated.
 
Promptly start prednisone 1 to 2 mg/kg/day PO or IV equivalent.
 
If event is not responsive within 3 to 5 days or worsens despite prednisone at 1 to 2 mg/kg/day PO or IV equivalent, additional workup should be considered and prompt treatment with IV methylprednisolone 2 to 4 mg/kg/day started.
 
Once the patient is improving, gradually taper steroids over <math>\geq 28</math> days and consider prophylactic antibiotics, antifungals, and anti-PJP treatment (refer to current NCCN guidelines for treatment of cancer-related infections).a
 
 |
| Rash or Dermatitis
(including Pemphigoid) | 
Any Grade
 (refer to NCI CTCAE v 5.0 for definition of severity/grade depending on type of skin rash)
                                                                                                      | 
General Guidance
                                                                                                                                                                                                                                         | 
For Any Grade:
 
 
Monitor for signs and symptoms of dermatitis (rash and pruritus).
 
IF THERE IS ANY BULLOUS FORMATION, THE STUDY PHYSICIAN SHOULD BE CONTACTED AND STUDY DRUG DISCONTINUED IF SUSPECT STEVENS-JOHNSON SYNDROME OR TOXIC EPIDERMAL NECROLYSIS.
 
                                                                                                                                                                                                                                                                                                                                                                                                                                                                          |
|                                                      | 
Grade 1
                                                                                                                                                                                                        | 
No dose modifications.
                                                                                                                                                                                                                                          | 
For Grade 1:
 
 
Consider symptomatic treatment, including oral antipruritics (e.g., diphenhydramine or hydroxyzine) and topical therapy (e.g., urea cream).
 
                                                                                                                                                                                                                                                                                                                                                                                                                                                                                                                                                                                            |
|                                                      | 
Grade 2
                                                                                                                                                                                                        | 
For persistent (<math>>1</math> to 2 weeks) Grade 2 events, hold scheduled study drug/study regimen until resolution to Grade <math>\leq 1</math> or baseline.
 
 
If toxicity worsens, then treat as Grade 3.
 
 | 
For Grade 2:
 
 
Obtain Dermatology consult.
 
Consider symptomatic treatment, including oral antipruritics (e.g., diphenhydramine or hydroxyzine) and topical therapy (e.g., urea cream).
 
Consider moderate-strength topical steroid.
 
                                                                                                                                                                                                                                                                                                                                                                                                                                                                                                  |

- If toxicity improves to Grade  $\leq 1$  or baseline, then resume drug/study regimen after completion of steroid taper.
- If no improvement of rash/skin lesions occurs within 3 to 5 days or is worsening despite symptomatic treatment and/or use of moderate strength topical steroid, consider, as necessary, discussing with study physician and promptly start systemic steroids such as prednisone 1 to 2 mg/kg/day PO or IV equivalent. If  $> 30\%$  body surface area is involved, consider initiation of systemic steroids promptly.
- Consider skin biopsy if the event is persistent for  $> 1$  to 2 weeks or recurs.

#### Grade 3 or 4

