**Inclusion Criteria:**

1. Written informed consent and any locally-required authorization obtained from the subject prior to performing any protocol-related procedures, including screening evaluations,
2. Male or female age  $\geq 18$  years at time of study entry,
3. Performance status of 0 or 1 according to the Eastern Cooperative Oncology Group (ECOG) and World Health Organisation (WHO),
4. Histologically confirmed diagnoses of colorectal cancer with positive mutated KRas or NRas
5. Patients with metastatic disease
6. First line metastatic disease **Or** First line after localized disease treated by local curative treatment, with or without adjuvant chemotherapy by FOLFOX; Recurrence after the last dose of adjuvant chemotherapy should be  $\geq 6$  months. Previous perioperative chemotherapy for resectable metastasis is not permitted
7. Life expectancy of  $> 12$  weeks,
8. Adequate normal organ and marrow function as defined below:
  - Haemoglobin  $> 9.0$  g/dL
  - Absolute neutrophil count (ANC)  $> 1.5 \times 10^9/L$  ( $>1500$  per  $mm^3$ )
  - Platelet count  $> 100 \times 10^9/L$  ( $\geq 100,000$  per  $mm^3$ )
  - Serum bilirubin  $\leq 1.5 \times$  institutional upper limit of normal (ULN).
  - AST (SGOT)/ALT (SGPT)  $\leq 2.5 \times$  institutional upper limit of normal unless liver metastases are present, in which case it must be  $\leq 5x$  ULN
  - PAL  $\leq 5 \times$  institutional upper limit of normal unless liver metastases are present, in which case it must be  $\leq 20x$  ULN
  - Albumin  $> 30g/L$
  - Creatinine  $< 1.5 \times$  institutional upper limit of normal (ULN)
  - Serum creatinine  $CL > 40$  mL/min by the Cockcroft-Gault formula (Cockcroft and Gault 1976) or by 24-hour urine collection for determination of creatinine clearance:

|                           | Males                                                                                     | Females                                                                                               |
|---------------------------|--------------------------------------------------------------------------------------------------|--------------------------------------------------------------------------------------------------------------|

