### 4.1 Inclusion criteria

For inclusion in the study, patients should fulfill the following criteria:

1. Written informed consent and any locally-required authorization obtained from the subject prior to performing any protocol-related procedures, including screening evaluations,

2. Male or female age  $\geq 18$  years at time of study entry,
3. Performance status of 0 or 1 according to the Eastern Cooperative Oncology Group (ECOG) and World Health Organisation (WHO),
4. Histologically confirmed diagnoses of colorectal cancer with positive mutated KRas or NRas.
5. Patients with metastatic disease
6. First line metastatic disease

**Or**

First line after localized disease treated by local curative treatment, with or without adjuvant chemotherapy by FOLFOX; Recurrence after the last dose of adjuvant chemotherapy should be  $\geq 6$  months. Previous perioperative chemotherapy for resectable metastasis is not permitted

7. Life expectancy of  $> 12$  weeks,
8. Adequate normal organ and marrow function as defined below:
  - Haemoglobin  $> 9.0$  g/dL
  - Absolute neutrophil count (ANC)  $> 1.5 \times 10^9/L$  ( $>1500$  per  $mm^3$ )
  - Platelet count  $> 100 \times 10^9/L$  ( $\geq 100,000$  per  $mm^3$ )
  - Serum bilirubin  $\leq 1.5 \times$  institutional upper limit of normal (ULN).
  - AST (SGOT)/ALT (SGPT)  $\leq 2.5 \times$  institutional upper limit of normal unless liver metastases are present, in which case it must be  $\leq 5 \times$  ULN
  - PAL  $\leq 5 \times$  institutional upper limit of normal unless liver metastases are present, in which case it must be  $\leq 20 \times$  ULN
  - Albumin  $> 30$ g/L
  - Creatinine  $< 1.5 \times$  institutional upper limit of normal (ULN)
  - Serum creatinine  $CL > 40$  mL/min by the Cockcroft-Gault formula (Cockcroft and Gault 1976) or by 24-hour urine collection for determination of creatinine clearance:

|                           | Males                                                                                     | Females                                                                                               |
|---------------------------|--------------------------------------------------------------------------------------------------|--------------------------------------------------------------------------------------------------------------|

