| 
PLEASE SEE shaded area immediately below this section to find guidance for management of “Hepatitis (elevated LFTS)” in HCC patients
 | Grade 1
(AST or ALT >ULN and $\leq 3.0 \times$ ULN if baseline normal, 1.5-3.0 $\times$ baseline if baseline abnormal; and/or TB >ULN and $\leq 1.5 \times$ ULN if baseline normal, >1.0-1.5 $\times$ baseline if baseline abnormal)                        | 
 
No dose modifications.
 
If it worsens, then treat as Grade 2.
 
                                                                                                                                                                                               | 
 
Continue LFT monitoring per protocol.
 
                                                                                                                                                                                                                                                                                                                                                                                                                                                                                                                                                                                                                                                                                                                                                                                                                                                                                                                                                                                                                                                |

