|                                                                                                                                                 | Grade 2
(AST or ALT >3.0 $\times$ ULN and $\leq 5.0 \times$ ULN if baseline normal, >3-5 $\times$ baseline if baseline abnormal; and/or TB >1.5 $\times$ ULN and $\leq 3.0 \times$ ULN if baseline normal, >1.5-3.0 $\times$ baseline if baseline abnormal) | 
 
Hold study drug/study regimen dose until resolution to Grade<math>\leq 1</math>.
 
If toxicity worsens, then treat as Grade 3.
 
If toxicity improves to Grade<math>\leq 1</math>, resume study drug/study regimen after completion of steroid taper.
 
 | For Grade 2: 
 
Regular and frequent checking of LFTs (e.g., every 1 to 2 days) until elevations of these are improving or resolved.
 
If no resolution to <math>\leq</math>Grade 1 in 1 to 2 days, consider, as necessary, discussing with study physician.
 
If event is persistent (>3 to 5 days) or worsens, promptly start prednisone 1 to 2 mg/kg/day PO or IV equivalent.
 
If still no improvement within 3 to 5 days despite 1 to 2 mg/kg/day of prednisone PO or IV equivalent, consider additional work up and start prompt treatment with IV methylprednisolone 2 to 4 mg/kg/day.
 
If still no improvement within 3 to 5 days despite 2 to 4 mg/kg/day of IV methylprednisolone, promptly start immunosuppressives (i.e., mycophenolate mofetil).a Discuss with study physician if mycophenolate mofetil is not available.
 Infliximab should NOT be used.
 
Once the patient is improving, gradually taper steroids over <math>\geq 28</math> days and consider prophylactic antibiotics, antifungals,
 
 |

and anti-PJP treatment (refer to current NCCN guidelines for treatment of cancer-related infections).a

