| 
Grade 3
 (AST or ALT >5.0×ULN and ≤20×ULN if baseline normal, >5-20× baseline if baseline abnormal; and/or TB >3.0×ULN and ≤10.0×ULN if baseline normal, >3.0-10.0× baseline if baseline abnormal)
 | 
For elevations in transaminases ≤8×ULN, or elevations in TB ≤5×ULN:
 
 
• Hold study drug/study regimen dose until resolution to Grade≤1
 
• Resume study drug/study regimen if elevations downgrade to Grade≤1 within 14 days and after completion of steroid taper.
 
• Permanently discontinue study drug/study regimen if the elevations do not downgrade to Grade≤1 within 14 days.
 
 
For elevations in transaminases >8×ULN or elevations in bilirubin >5×ULN, permanently discontinue study drug/study regimen.
 | 
For Grade 3 or 4:
 
 
– Promptly initiate empiric IV methylprednisolone at 1 to 4 mg/kg/day or equivalent.
 
– If still no improvement within 3 to 5 days despite 1 to 4 mg/kg/day methylprednisolone IV or equivalent, promptly start treatment with immunosuppressive therapy (i.e., mycophenolate mofetil). Discuss with study physician if mycophenolate is not available. Infliximab should NOT be used.
 
– Request Hepatology consult, and perform abdominal workup and imaging as appropriate.
 
– Once the patient is improving, gradually taper steroids over ≥28 days and consider prophylactic antibiotics, antifungals, and anti-PJP treatment (refer to current NCCN guidelines for treatment of cancer-related infections).a
 
 |

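### Appendix 1 hepatitis table: severity is read on baseline but the Grade 3 action on ULN, so the transaminase hold-and-resume limb cannot be reached by patients entering with AST/ALT at or above 1.6×ULN

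*Protocol*

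**What the plan says.** The liver-function item of the inclusion criteria (Protocol, Synopsis and Section 4.1) caps AST/ALT at 2.5×ULN "unless liver metastases are present, in which case it must be" at or below 5×ULN. Patients with clearly raised transaminases are therefore eligible.

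Appendix 1, Hepatitis (elevated LFTs), defines severity for these patients relative to their own baseline:

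- Grade 1: "1.5-3.0 $\times$ baseline if baseline abnormal". The action is "No dose modifications", followed by "If it worsens, then treat as Grade 2".
- Grade 2: above the lower figure in "3-5 $\times$ baseline if baseline abnormal". The action is to hold, then to resume once the event is back to Grade 1 or less and the steroid taper is complete.
- Grade 3: above the lower figure in "5-20× baseline if baseline abnormal".

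The Grade 3 action cell then changes scale. One branch (hold, and resume if the value falls to Grade 1 or less within 14 days) is introduced by "For elevations in transaminases ≤8×ULN, or elevations in TB ≤5×ULN". The other, permanent discontinuation, applies to transaminases above 8×ULN or bilirubin above 5×ULN. No sentence connects the two scales. The later hepatitis rows that combine baseline and ULN limits are marked as applying only to HCC patients.

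**The concern.** When one row states its severity range in multiples of baseline and its action limits in multiples of ULN, the two agree only if baseline is close to ULN. This protocol deliberately admits patients whose baseline is not. For them, a step that the table offers (Grade 3, hold and resume) may not exist for transaminases, while quite high absolute values carry a lower grade and a milder action.

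Safety of the combination is the phase Ib primary objective, and hepatitis or transaminase increase is a listed event of special interest in Section 10.1.3. At stake is whether sites can apply the hepatic dosing rule to patients with raised baseline enzymes in the way its authors meant.

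**Working it through.** The protocol states no figure to reproduce. The check puts both scales into ULN units.

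**Inputs.** Let b be baseline AST/ALT in multiples of ULN. Entry allows b ≤ 2.5, or b ≤ 5 with liver metastases (Section 4.1). From Appendix 1, for abnormal baseline, the top of Grade 1 is 3b, the top of Grade 2 is 5b, and Grade 3 is above 5b up to 20b. For normal baseline, Grade 3 is above 5 up to 20×ULN. The Grade 3 hold limit is 8×ULN.

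**Transaminase hold window.** A value must be Grade 3 (above 5b) and at most 8×ULN. The window is empty when 5b ≥ 8, that is b ≥ 8/5 = 1.6.

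| Baseline (×ULN) | Top of Grade 1 | Top of Grade 2 | Grade 3 hold window (×ULN) |
|---|---|---|---|
| normal | 3 | 5 | above 5 to 8 |
| 1.2 | 3.6 | 6 | above 6 to 8 |
| 1.5 | 4.5 | 7.5 | above 7.5 to 8 |
| 1.6 | 4.8 | 8 | empty |
| 2.5 | 7.5 | 12.5 | empty |
| 4 | 12 | 20 | empty |
| 5 | 15 | 25 | empty |

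The empty range therefore covers baselines from 1.6 to 2.5×ULN without liver metastases and from 1.6 to 5×ULN with them.

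**Values above 8×ULN in lower grades.** They can be Grade 2 once 5b > 8 (b > 1.6). They can be Grade 1 once 3b > 8 (b > 8/3 ≈ 2.67), which is eligible only with liver metastases.

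**Example, b = 4.** Grade 1 runs from 1.5 × 4 = 6 to 3 × 4 = 12×ULN inclusive, with no dose modification. Grade 2 runs above 12 to 5 × 4 = 20×ULN, with a hold. Grade 3 starts above 20×ULN, already past 8×ULN, so the only Grade 3 action is permanent discontinuation. With a normal baseline, everything above 8 and up to 20×ULN is Grade 3 with permanent discontinuation.

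**Bilirubin limb.** Grade 3 by total bilirubin starts above 3×ULN with normal baseline. At the entry limit of 1.5×ULN it starts above 3 × 1.5 = 4.5×ULN. Both lie below the 5×ULN hold limit, so this limb is not empty.

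**Other rules that might fill the gap.** The Hy's law clause in the table needs bilirubin above 2×ULN as well as AST/ALT above 3×ULN. The hepatic function abnormality rule (Sections 10.1.3 and 10.2.3.2) also needs bilirubin above 2×ULN. Neither reaches an isolated transaminase rise.

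**The case against.** The strongest reply is that the table can be applied as it stands. A value is graded first and then that row's action is read, and the 8×ULN stop is printed only inside the Grade 3 cell. At b = 4 this gives no change up to 12×ULN, hold above 12 to 20, and discontinue above 20: one action per value, in a sensible order. Grading relative to baseline is written into every severity row, so different actions at the same absolute value are partly by design. Section 6.2.1 also calls for clinical judgment beyond the guidelines in rapidly progressing or high-risk events. All of this stands, and it rules out any claim that the rows order contradictory actions for one value. It does not explain why the Grade 3 cell offers a transaminase branch that these patients cannot enter.

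A reader might infer more than the protocol supports:

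- *That the whole hold branch is dead for these patients.* It is not. A patient can be Grade 3 through bilirubin at or below 5×ULN and be held, unless Hy's law is met; cholestasis or an alternative cause would take the case out of that clause.
- *That 12×ULN at baseline 4×ULN shows no response to a serious rise.* It is the exact top of Grade 1. Anything higher is a Grade 2 hold, and the Grade 1 cell carries its own note on worsening.
- *That reported hepatic grade counts are distorted.* Sections 6.2.1 and 10.1.5 grade toxicity by CTCAE v4.03. The v5.0 grades in Appendix 1 govern drug administration, and nothing shows that they feed the safety tables.
- *That half or more of patients are affected.* The 50-70% in the Introduction is the frequency of liver localisation among patients with metastases, not of entry AST/ALT at or above 1.6×ULN.

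**Conclusion.** The point holds for transaminases. For every eligible baseline of 1.6×ULN or more, the transaminase limb of the Grade 3 hold-and-resume branch is unreachable, and the path runs from the Grade 2 hold directly to permanent discontinuation. Over the same baselines, some values above 8×ULN are Grade 2, and above a baseline of about 2.67×ULN some are Grade 1. The gap concerns isolated transaminase rises.

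The conclusion rests on the printed thresholds, on reading severity before action, and on the HCC rows not applying to this population. How many patients it touches cannot be derived, because the protocol gives no distribution of baseline AST/ALT. It is a safety rule that does not work as written for some admitted patients and deserves correction. It does not affect the efficacy design.

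**What to change.** The sponsor's safety physicians should reconcile the baseline-referenced severity definitions in the Hepatitis (elevated LFTs) rows of Appendix 1 with the ULN-based action limits in the Grade 3 cell, for patients who enter with abnormal AST/ALT. They should state whether the 8×ULN limit is meant to apply to these patients. No threshold and no choice of reference scale is proposed here.

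The change needs no new data or visits. It is a clarification to a few table cells. Because Appendix 1 is a general durvalumab/tremelimumab guideline with paediatric and HCC parts, a trial-specific note may have to be agreed with the drug supplier.
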